## Abstract

**Background:**

Allergic rhinitis (AR) is the inflammation of the membranes lining the nose due to allergen exposure and is characterized by sneezing, nasal congestion, itching of the nose, or postnasal discharge. The prevalence varies worldwide, perhaps due to the geographic and aeroallergen differences, with 10% to 30% of the world’s population experiencing AR. In this study, Anu Taila Nasya, Naradiya Laxmivilas Rasa, and Shirishadi Kwath will be compared to a fluticasone nasal spray.

**Objective:**

The primary aim is to assess the efficacy of Ayurvedic management for AR (or vataja pratishyaya) by comparing it to a conventional control group. The secondary aims are to determine the mean change in the nasal endoscopy index and the mean change in the laboratory tests.

**Methods:**

This ongoing study is an open-label randomized controlled interventional trial, with a sample size of 90 both in the trial and standard control group (including dropouts, 20%), and will be carried out for 24 months. Participants in the trial group will receive Ayurvedic treatment, that is, Anu Taila Nasya (6 drops in each nostril for 7 days for 3 consecutive weeks), Naradiya Laxmivilas Rasa (250 mg twice per day), and Shirishadi Kwath (40 ml twice per day for 45 days). The participants in the control group will receive a fluticasone propionate nasal spray (2 sprays once per day for 45 days). The primary outcome will include the mean change in the Control of Allergic Rhinitis and Asthma Test score, and the secondary outcomes will include the mean change in the nasal endoscopy index (assessment of nasal membrane color, pale or hyperemia; rhinorrhea, watery or yellow; and inferior turbinate swelling, hypertrophy) and the mean change in the laboratory tests.

**Results:**

As of May 2024, 72 patients have been enrolled in both groups. Data analysis should be completed by February 2025. The study will be reported following standard guidelines for reporting randomized controlled trials. Clinical results will be disseminated through conferences and peer-reviewed publication in a relevant journal.

**Conclusions:**

The Ayurvedic approach could be an evidence-based therapeutic tactic for the management of AR.

**Trial Registration:**

Clinical Trials Registry India CTRI/2023/06/053395; https://tinyurl.com/564d2zz8

**International Registered Report Identifier (IRRID):**

DERR1-10.2196/56063

## Introduction

Allergic rhinitis (AR), a heterogeneous disorder, often remains undiagnosed despite its high prevalence. It is characterized by one or more of the following symptoms: sneezing, itching, nasal congestion, and rhinorrhea [1]. The nose is exposed to a variety of microorganisms, allergens, and environmental pollutants present in the atmosphere because of its direct contact with the external environment. If the early stage of AR is not adequately treated, it causes mucosal changes in nostrils and results in turbinate hypertrophy, nasal polyps, allergic bronchitis, etc. AR is the inflammation of the membranes lining the nose due to an allergen exposure [2].

AR affects 26% of the population in India [3]. The prevalence of AR has increased significantly in some countries, but national trends are inconsistent [4]. AR is the most common atopic condition, affecting about 10%-30% of adults and up to 40% of children worldwide [5]. In India, its prevalence has gradually risen in the last 2 decades [6]. The diagnosis is based on clinical manifestations and supported by positive results from a skin prick test or demonstration of serum-specific immunoglobulin E antibodies to aeroallergens or direct nasal endoscopy.

In this study, the diagnosis of AR and its classification into mild and moderate-severe groups were made according to the Allergic Rhinitis and Its Impact on Asthma (ARIA) classification [7]. The cardinal symptoms, according to ARIA guidelines, are paroxysmal sneezing; itching in the nose; itching of the eyes, palate, or pharynx; watery nasal discharge; nasal obstruction; and history of urticaria, while the clinical signs include pale boggy nasal mucosa; hypertrophied turbinates; thin, watery, or mucoid discharge; allergic shiner; and transverse nasal crease (allergic salute) [8]. The control group was selected as per ARIA guidelines.

The lack of curative treatment necessitates other systems of health providing remedial treatment, such as Ayurvedic science. As treatments with standard medications have their own limitations, there is scope for using Ayurveda, which emphasizes a holistic approach to every disease based on the Doshas (psychobiological rhythm: vata, pitta, and kapha), Dhatus (body tissues and their nourishing elements), and malas (excreta). In Ayurveda, AR is similar to vataja pratishyaya [9], and as per the Ayurvedic literature, it is a curable disease [10]. There are few published preclinical and clinical studies proving the efficacy of Ayurveda interventions, such as Rajanyadi Churna and Guduchi Kwath [11], Ayurvedic herbo-mineral formulation IMMBO [12], Triphala [13], Haridra Khanda and Manjisthadi Kwath (brihat) [14], Tamalakyadi decoction [15], and Haridra Khanda and Pippalyadi Taila [16].

One study was carried out at the Institute of Post Graduate Teaching and Research in Ayurveda, Jamnagar [17], and one pilot study was also conducted at the Central Council for Research in Ayurvedic Sciences (CCRAS) studying an Ashwagandhadi compound, Shirishadi Kwath, and Anu Taila Nasya (intranasal drug administration), which found significant results [18]. Naradiya Laxmivilas Rasa’s (NLR) use for respiratory disorders has previously been discussed in Ayurvedic literature [19]. No randomized controlled trial studies have been published comparing NLR, Shirishadi Kwath, and Anu Taila Nasya to a fluticasone nasal spray used in an allopathic system as per standard treatment for patients with AR. Considering these facts, a randomized controlled trial has been proposed here.

## Methods

### Study Objectives

The primary objective is to assess the efficacy of Ayurvedic management for AR (vataja pratishyaya) by comparing it with a conventional control group. The secondary objectives are to determine the mean change in the nasal endoscopy index (assessment of nasal membrane color, pale or hyperemia; rhinorrhea, watery or yellow; and inferior turbinate swelling, hypertrophy) [20] and mean change in the laboratory tests.

### Study Setting

This study will be conducted at Vardhman Mahavir Medical College and Safdarjung Hospital, New Delhi, India.

### Eligibility Criteria

#### Inclusion Criteria

Patients of either sex between the ages of 18 and 65 years with intermittent or persistent AR (as per the internationally recognized ARIA diagnostic standard) who were diagnosed based on their medical history and who were willing to participate and provide informed consent were eligible for the study.

#### Exclusion Criteria

The following exclusion criteria were used: patients who had a history of chronic nasal or upper respiratory tract symptoms or disorders other than AR, non-AR chronic sinusitis, or serve bronchial asthma with nasal anatomical defects (grossly deviated nasal septum), nasal polyposis, tonsillitis, or airway obstructions (adenoids); patients with a nasal condition likely to affect the outcome of the study; patients receiving any treatment of H1 antihistamine medication or nonsteroidal analgesics; patients using corticosteroids nasal drops, leukotriene antagonists, or nasal vasoconstrictors; patients who have received a surgical procedure on the nose like septoplasty/submucous resection, inferior turbinate reduction, or endoscopic sinus surgery; women who are pregnant and lactating mothers; patients with any debilitating chronic disease (eg, tuberculosis or uncontrolled diabetes mellitus), any unstable cardiovascular diseases, evidence of malignancy, concurrent hepatic disorder (defined as aspartate amino transferase or alanine amino transferase >2 times the upper normal limit) or renal disorders (defined as *S creatinine* greater than the upper limit of laboratory value), pulmonary dysfunction (bronchial asthma or chronic obstructive pulmonary disease), or acute mental disorder; and patients who are currently participating in any other clinical trial.

### Study Interventions (Investigational Products)

Participants in the treatment group will undergo Nasya therapy for 7 days for 3 consecutive cycles. Along with the Nasya therapy, the participants will receive a 250 mg dose of NLR twice daily after meals with lukewarm water and 40 ml of Shirishadi Kwath twice daily on an empty stomach for 45 days. In the standard control group, participants will receive a 200 mcg dose of fluticasone propionate nasal spray (50 mcg/spray) per day (2 puffs once daily) for 45 days. The treatment group medicine (investigational products) will be procured from good manufacturing practice–certified pharmacies through the Indian Medicines Pharmaceutical Corporation Limited (Mohaan) and the Central Ayurveda Research Institute (Jhansi), along with a certificate of analysis to ensure the investigational products’ quality standards and safety. The control group’s medicine will be procured from a good manufacturing practice–certified government agency. The study drugs will be kept in a secure place and will only be supplied to the participants under the guidance of the investigator. A record will be maintained for the drug dispensed. Any discrepancies between the amounts dispensed and returned will be explained.

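### The printed fluticasone regimen does not multiply out: 2 sprays of 50 mcg once daily give 100 mcg, not the stated 200 mcg, and a per-nostril term is probably missing

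*Protocol article*

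**What the plan says.** The control regimen is described in two places in the protocol article.

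- **Methods, Study Interventions (Investigational Products):** a "200 mcg dose of fluticasone propionate nasal spray (50 mcg/spray) per day (2 puffs once daily) for 45 days". This one sentence gives the daily total, the strength per spray, the number of sprays and the frequency.
- **Abstract, Methods:** "fluticasone propionate nasal spray (2 sprays once per day for 45 days". It has the same count and frequency, with no strength and no total.

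Fluticasone is also named in the Abstract's Background ("will be compared to a fluticasone nasal spray") and in the Introduction ("to a fluticasone nasal spray used in an allopathic system as per standard treatment for patients with AR"), both times without a dose.

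A dose per nostril appears only for the Ayurvedic nasal drops, in the Abstract: "6 drops in each nostril for 7 days for 3 consecutive weeks". The Study Interventions section shortens that regimen too: "Participants in the treatment group will undergo Nasya therapy for 7 days for 3 consecutive cycles". The only other mention of nostrils is disease background in the Introduction.

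**The concern.** The Study Interventions sentence prints four facts about the control dose, and they cannot all be true if the puffs are a daily total. The count implies half the stated number of micrograms. The Abstract does not settle the matter, because it repeats the count without the other figures.

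Fluticasone is the sole comparator and is presented as standard treatment, so the trial's main contrast is Ayurvedic management against this regimen. If the count were followed literally, the active control would run at half its stated dose. Assuming the lower dose works less well, which the documents do not address, that would tilt the comparison towards the Ayurvedic arm. The prescribed quantity is also the natural reference for judging adherence from the amount consumed, and the Drug Compliance section makes 80% compliance the condition for continuing.

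**Working it through.** **Inputs**, all from Study Interventions (Investigational Products); the Abstract repeats the count, frequency and duration:

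- stated daily dose: 200 mcg
- strength: 50 mcg per spray
- count: 2 puffs
- frequency: once daily
- duration: 45 days

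**Formula.** Daily dose = mcg per spray × sprays per administration × administrations per day (× 2 if the count is per nostril).

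**Step 1: try to reproduce the stated 200 mcg.** As printed, 50 × 2 × 1 = 100 mcg/day. The ratio to the stated dose is 100 / 200 = 0.5, so the figure is not reproduced.

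**Step 2: sprays needed for the stated dose.** 200 / 50 = 4 sprays a day, against 2 printed.

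**Step 3: which reading would reconcile the figures?**

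| Reading | mcg/day | Agrees with all four printed figures? |
|---|---|---|
| 2 sprays in total, once daily | 2 × 50 = 100 | No, total is half |
| 1 spray per nostril, once daily | 1 × 2 × 50 = 100 | No, total is half |
| 2 sprays per nostril, once daily | 2 × 2 × 50 = 200 | Yes |
| 2 sprays in total, twice daily | 2 × 2 × 50 = 200 | No, contradicts once daily |
| 2 sprays of 100 mcg, once daily | 2 × 100 = 200 | No, contradicts 50 mcg per spray |

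Of the readings tried, only 2 sprays per nostril keeps the total, strength, count and frequency as printed, and it needs a word that the article does not contain.

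**Step 4: size over the course.**

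- Literal count: 2 × 45 = 90 sprays, or 90 × 50 = 4,500 mcg.
- Per nostril: 4 × 45 = 180 sprays, or 180 × 50 = 9,000 mcg.
- 80% compliance threshold: 0.8 × 90 = 72 sprays, against 0.8 × 180 = 144.
- A participant who used 90 sprays would be 90 / 90 = 100% compliant on the literal count and 90 / 180 = 50% compliant on the per-nostril reading.

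The sample size calculation uses only the CARAT difference, the SD, the error rates and the dropout rate. None of these depends on the spray count.

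**The case against.** The strongest reply is that this is an abbreviation and not a wrong dose. The total and the strength are explicit, a nasal spray is ordinarily divided between two nostrils, and the per-nostril reading makes every printed figure agree. To arrive at 100 mcg, a reader must override the stated total. The same section also drops the nostril detail for the Nasya drops, which points to routine shortening, and a journal article may fairly leave administration detail to the full protocol. Figure 1, which sets out the study procedure, was not available for review and might carry the missing words. As for compliance, both thresholds are 80% of whatever was prescribed, and nothing suggests that site staff used the wrong denominator.

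Much of this stands. The omitted term is much the likeliest cause, there is no evidence of underdosing, and the compliance consequence is only potential. It does not make the sentence correct. Leaving detail out is acceptable in an article, but here the article chose to print total, strength, count and frequency, and they disagree as written. The shortened Nasya text leaves no conflicting figures; the fluticasone text does. If Figure 1 does carry the nostril term, the sentence in Study Interventions would still need correcting.

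**Conclusion.** The concern holds, as a minor point. The stated control dose is twice what the printed count delivers: 200 against 100 mcg/day, or 4 sprays needed against 2 printed. The arithmetic needs no outside assumption beyond reading the puffs as a daily total, which is what the words say.

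That a per-nostril term was omitted is an inference. It is well supported, because no other reading tried preserves all the figures, but the text does not exclude the alternative that 2 sprays in total is intended and the 200 mcg is wrong. Until that is settled, the comparator regimen cannot be taken unambiguously from the article. Design, sample size, power and analysis are unaffected.

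**What to change.** In both the Abstract and Study Interventions, state the regimen as 2 sprays (50 mcg each) in each nostril once daily, total 200 mcg/day, for 45 days. If 2 sprays overall is truly intended, change the total to 100 mcg/day instead.

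Confirm that the participant instructions carry the same regimen and that the quantity used to judge compliance matches it (180 sprays over the course at 4 a day, or 90 at 2 a day). Report the dose actually used with the results; this matters because recruitment is already under way.

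The cost is a wording correction in two places and one check of the participant instructions and compliance reference, with no change to design, sample size or analysis.

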### Strategies to Improve Adherence to the Study Protocol

Medication adherence will be assessed at each follow-up visit (days 16, 31, 45, 75, 105, and 135) by assessing the approximate quantity consumed. The participant will be asked to return the empty medicine container at each follow-up visit. Repeated phone reminders to regularly take the medicine from project staff will be given to the participants or their family members.

### Outcome Measures

#### Primary Outcome Measure

The primary outcome measure is the mean change in the Control of Allergic Rhinitis and Asthma Test (CARAT) score [21] at baseline and days 16, 31, 45, 75, 105, and 135. The CARAT questionnaire comprises 10 questions about upper and lower airway symptoms, sleep interference, activity limitation, and the need to increase medication over a 4-week period (Multimedia Appendix 1, also available on the web [22]). The total possible score ranges from 0 (minimum control) to 30 (maximum control) [21].

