### Sample Size

In a previous pilot study on this Ayurvedic intervention, a change of 14 points in the CARAT score was observed. For this study, it was assumed that a change of 10 points would be seen in the placebo group. With an SD of 6 points based on the results of the previous pilot study, a sample size of 35 participants per group was calculated to provide 80% power, with a 95% CI.

Assuming a dropout rate of 20%, a total of 90 participants, 45 per group, will be included in this trial.

n_1_ = n_2_ = 2 *σ*^2^ [(Z_1 – α/2_) + (Z_β_)]^2^ ÷ Δ^2^

n_1_ = n_2_ = 2 * (6)^2^ [(1.96 + 0.84)]^2^ ÷ (4)^2^

n_1_ = n_2_ = 35

where Δ is |μ_2_ – μ_1_| (the absolute difference between two means), σ is the variance of two means, n_1_ is the sample size for group 1, n_2_ is the sample size for group 2, α is the probability of type 1 error (usually .05), β is the probability of type 2 error (usually .2), and z is the critical *Z* value for a given α or β.

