### Study Procedure

The participant will be screened for AR as per the inclusion criteria. Prior to any trial-related activity, the investigator will give the participants or their parents or guardians information about the trial verbally and in printed form. The investigator will ensure that the participant is fully informed about the aims, procedures, discomforts, and expected benefits of the trial. It must be emphasized that participation is voluntary, and participants have the right to discontinue the trial at any time without any prejudice.

After the screening, suitable participants will be enrolled in the study after signing the consent form. The required tests will be carried out. Within 1 week or as soon as the laboratory results are received and found to be within the eligibility limits, the participant will be enrolled in the study, with this day being recorded as visit 1 or the baseline visit. The treatment will be given to her after fulfilling all the formalities as per the protocol. The subsequent follow-up will be on day 16 (visit 2), day 31 (visit 3), day 45 (visit 4), day 75 (visit 5), day 105 (visit 6), day 135 (visit 7), and completion of the active treatment (visit 8). Participants will visit the study site 8 times during the trial. The activity details during each visit are presented in Table 1 and Figure 1.

**Table 1 table1:** Study schedule.

Component	Screening	Baseline	Days 16 and 31	Day 45	Days 75 and 105	Day 135
Informed consent	✓					
Demographics and medical history		✓				
Assessment of Prakriti		✓				
Laboratory tests	✓			✓		
Clinical examination		✓	✓	✓	✓	✓
Assessment of Ayurvedic parameters		✓		✓	✓	✓
Concomitant medication		✓	✓	✓		
Rescue medication			✓	✓		
Assessment of adverse drug reactions			✓	✓		
Assessment of drug compliance			✓	✓		
Issue of trial drugs		✓	✓			
Control of Allergic Rhinitis and Asthma Test score	✓			✓		
Diagnostic nasal endoscopy		✓		✓		✓

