### Statistical Methods

Continuous variables will be presented as means, SDs, medians, and ranges. Categorical variables will be summarized with frequencies and percentages. When inferential analyses are conducted for continuous variables, they will be tested for normality. Nonparametric methods will be used for comparison of nonnormal data. Within-group comparisons will be done by using paired *t* tests, while between-group comparisons will be done using independent sample *t* tests for the data with normal distribution. Nonnormal data within the group will be compared using the Wilcoxon sign rank test, while between-group comparisons will be done by using the Mann-Whitney *U* test. Categorical data between groups will be compared using the *χ*^2^ or Fisher exact test. A 2-sided *P* value <.05 will be considered statistically significant. Per-protocol and intention-to-treat analyses will be carried out at the end of the study. All data will be analyzed using STATA 16.1 (StataCorp).

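### The primary CARAT outcome has no named primary visit, and its six post-baseline time points contradict Table 1, which schedules CARAT only at screening and day 45

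*Protocol article*

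**What the plan says.** The protocol article describes the primary outcome in several places.

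- **Primary Outcome Measure:** mean change in the CARAT "score [21] at baseline and days 16, 31, 45, 75, 105, and 135". That is a baseline and six post-baseline visits, with none marked as primary. The same section says the questionnaire looks back over 4 weeks ("the need to increase medication over a 4-week period").
- **Abstract, Methods:** "The primary outcome will include the mean change in the Control of Allergic Rhinitis and Asthma Test score", with no time point.
- **Study Procedure, Table 1:** the row "Control of Allergic Rhinitis and Asthma Test score" is ticked under Screening and under Day 45 only. The cells for Baseline, Days 16 and 31, Days 75 and 105, and Day 135 are empty.
- **Sample Size:** one contrast. For the Ayurvedic arm, "a change of 14 points in the CARAT score was observed"; 10 points are assumed for the comparator, with an SD of 6. No visit is attached to either figure.
- **Statistical Methods:** "between-group comparisons will be done using independent sample" t tests, or Mann-Whitney if the data are not normal. A two-sided P "value <.05 will be considered statistically significant". No longitudinal model, order of testing or rule for combining visits is given.

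Treatment lasts 45 days (Study Interventions). Strengths and Limitations describes a further 90 days of follow-up intended to detect recurrence.

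**The concern.** A primary outcome needs a measure and a time. Here the measure is clear and the time is not. The outcome section gives six candidate times, the schedule supports one, and the abstract and sample size give none.

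Two different things are at stake, depending on which passage staff and analysts follow.

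- **If sites follow Table 1,** most of the stated primary outcome is never collected, and the recurrence follow-up has no data on the primary instrument. No later analysis plan can recover questionnaires that were not administered.
- **If the outcome section governs,** the analyst has six between-group comparisons and no stated rule for which one decides the trial. The visits do not answer one question: days 16 and 31 are during treatment, day 45 is its end, and days 75, 105 and 135 concern persistence after it. In an open-label trial whose authors already expect the treatment arm to do better (Strengths and Limitations), an unnamed primary visit leaves room for choosing it after results are seen.

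**Working it through.** **1. Outcome section against Table 1.**

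- Day 16: outcome section yes, Table 1 no
- Day 31: yes, no
- Day 45: yes, yes
- Day 75: yes, no
- Day 105: yes, no
- Day 135: yes, no
- Reference value: baseline in the outcome section, screening in Table 1

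The schedule therefore supports 1 of 6 post-baseline values and loses 5. All three post-treatment visits are among those lost. A text-extraction fault is unlikely, though it cannot be ruled out: the CARAT row has the same tick pattern as the laboratory row, and neighbouring rows (clinical examination, nasal endoscopy) do carry ticks at later visits.

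**2. The plan's own sample size.** Inputs from Sample Size: difference 14 − 10 = 4, SD 6, z values 1.96 and 0.84.

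- n per group = 2 × 6² × (1.96 + 0.84)² ÷ 4² = 2 × 36 × 7.84 ÷ 16 = 35.28. The plan gives 35; rounded up it is 36.
- With 20% dropout: 36 ÷ 0.8 = 45 per group, 90 in total, as stated.
- Power for one test at two-sided 0.05: 80.7% with 36 per arm, 88.5% with 45 per arm.

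The calculation is reproduced, and it is for one comparison at 0.05.

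**3. Error rate if any of six visits may count.** The documents give no between-visit correlation, so this is an assumption shown over a range. Simulating six equally correlated two-sided null z tests (1,000,000 draws), the chance that at least one exceeds 1.96 in absolute value is:

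- correlation 0.3: 24.1%
- 0.5: 20.7%
- 0.7: 16.4%
- 0.8: 13.8%
- 0.9: 10.8%

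Independent tests would give 1 − 0.95⁶ = 26.5%, an upper figure that does not suit repeated measures on the same patients.

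For change scores, 0.5 is a natural lower end. If all raw scores have equal variance and equal correlation r, two changes from a shared baseline have covariance proportional to 1 − r and variance proportional to 2(1 − r), so their correlation is (1 − r) ÷ 2(1 − r) = 0.5 whatever r is. It is higher if post-baseline scores correlate more with each other than with baseline; unequal variances could lower it. The working range is therefore 0.5 to 0.9, or about 21% down to 11%.

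**4. Cost of keeping six co-equal tests.** Bonferroni at 0.05 ÷ 6 with 80% power needs 55 per arm, and 55 ÷ 0.8 = 68.75, so 69 with dropout. The planned 36 and 45 per arm would give 57.5% and 70.0% power.

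**5. Recall window.** If treatment starts at the baseline visit, the day-16 score covers 28 − 16 = 12 pre-treatment days, 12 ÷ 28 = 43% of the window. The day-45 window reaches back to about day 17 (45 − 28) and lies wholly within treatment.

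**The case against.** The strongest reply is that the two passages cannot both produce harm. If Table 1 governs, there is one day-45 comparison and no multiplicity across visits. Inflation needs the outcome section to govern and any significant visit to count as success, and the protocol says neither. The outcome section may simply list measurement times, Statistical Methods is a general list of tests, and Sample Size rests on one contrast, which suggests that one comparison was intended. Decision rules are also commonly left to an analysis plan, which is not shown here. All of this stands. A reader might infer that the trial's type I error is inflated as designed; the documents do not establish that.

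Two lesser inferences also go too far.

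- **That no baseline CARAT exists.** Table 1 ticks laboratory tests only at screening as well, yet Secondary Outcome Measures and Laboratory Tests call those values baseline. The screening CARAT may well serve the same purpose. The label needs settling; a missing baseline is not shown.
- **That four-week recall biases the day-16 result.** Pre-treatment days enter both randomized arms alike. They dilute a difference but neither bias the comparison nor raise type I error.

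What the reply does not remove is the contradiction in the protocol itself. An analysis plan can add a testing rule but cannot supply uncollected data, and the time points of the primary outcome are stated here in conflict rather than left for later.

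**Conclusion.** The point holds as an inconsistent and incompletely defined primary endpoint. Two findings are firm and need no assumption: no primary visit is named, and the outcome section and Table 1 disagree on five of six post-baseline time points and on which pre-treatment score is the reference.

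The size depends on which passage is followed. Under Table 1, five of six primary values and all CARAT data for the 90-day recurrence follow-up are lost. Under the outcome section, with any visit at P<.05 allowed to count and no adjustment elsewhere, family-wise error is about 11% to 21%, or about 24% at a correlation of 0.3, against 5%. Those rates rest on assumed equal correlations and on a success rule that the protocol does not state.

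The recall period is only a supporting reason for not making day 16 primary. Correction is needed before analysis, because the ambiguity concerns the result on which the trial will be judged.

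**What to change.** - Name change in CARAT from baseline to day 45 as the single primary endpoint, tested between groups at two-sided 0.05. Day 45 is the end of treatment and the only post-baseline visit on which the outcome section and Table 1 agree.
- Make all other CARAT visits secondary. A longitudinal model with a prespecified day-45 contrast would serve equally well.
- Correct Table 1 and the case report form so that CARAT is ticked at every retained visit, and state whether the screening or the baseline-visit score is the reference.
- Record when and by whom (by role) the primary visit was chosen, and that it was chosen without sight of outcome data by arm. This matters because the trial is open-label, 72 of 90 participants (80%) were enrolled by May 2024, and a safety analysis is planned after 25% complete.
- Report how many CARAT assessments were missed because Table 1 was followed, and say that they cannot be recovered.

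The cost is an amendment, a schedule and form correction, and a 10-item questionnaire at visits already planned. Alpha stays at 0.05 and no participants need be added.
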